## 2.2 Secondary Objectives

The following objectives are to compare between a personalized treatment of iMN driven by anti-PLA2R1 antibody epitope profiles and the GEMRITUX therapeutic protocol:

1. Complete clinical remissions at M6, M9, M12, M18, M24
2. Partial clinical remission at M6, M9, M12, M18, M24
3. Immunological remissions at M6, M9, M12, M18, M24
4. Proteinuria and albuminuria at M6, M9, M12, M18, M24
5. Changes in proteinuria and albuminuria from baseline at M6, M9, M12, M18, M24
6. Serum creatinine and estimated glomerular filtration rate (eGFR) at M6, M9, M12, M18
7. Changes in serum creatinine and eGFR from baseline at M6, M9, M12 and M18
8. PLA2R1-Ab titers at M6, M9, M12, M18 and M24
9. Recording all AEs/SAEs during study follow-up, 24 months

The following objectives aim to study risk factors for remission or relapse:

10. To determine risk factors for remission (immunological and clinical, partial or complete) at M12 in patients pooled from the two arms
11. To determine risk factors for relapse (between M12 and M24) in patient responders at M12, pooled from the two arms

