## 3. Evaluation criteria

### Principal evaluation criteria:

Clinical remission will be defined as a composite criterion combining (KDIGO definitions):

- Complete clinical remission: urinary protein/creatinine ratio (UPCR)<0.3 g/g in spot morning urine samples and Normal serum albumin and eGFR > 60 ml/min/1.73 m^2

- Partial clinical remission: UPCR < 3.5 g/g with a decrease greater than 50% from baseline and improvement or normalization of the serum albumin concentration and increase of serum creatinine lower than 20%

Secondary evaluation criteria:

1. Complete clinical remission as defined above
2. Partial clinical remission as defined above
3. Immunological remission: full PLA2R1 depletion measured by ELISA (titer<14RU/ml)
4. Proteinuria and albuminuria are measured on urine sample (proteinuria-to-creatinine ratio or albuminuria-to-creatinine ratio g/g) or collected during one day (g per day)
5. Change in proteinuria are measured in percentage change in proteinuria from baseline to M6, M9, M12, M18, M24
6. Serum creatinine is measured in blood sample in  $\mu\text{mol/l}$  and eGFR using the CKD-EPI formula.
7. Change in serum creatinine and eGFR are measured in percentage change from baseline to M6, M9, M12, M18, M24
8. PLA2R1-Ab titer are measured by ELISA in RU/ml
9. Severe infections are defined as infections that led to hospitalization during study follow-up
10. Remission will be defined as already stated. Patients from both groups will be analysed jointly. The following risk factors will be studied in this analysis:
  - Lymphocyte counts: B cells (CD19, transitional, mature and memory) and T cells (CD3, CD4, CD8 and TReg) measured in blood sample at J0, M3, M6, post-rituximab infusion
  - Serum level of cytokines (pg/ml) measured in blood sample at J0, and after first remission (or M24 if no remission)
  - Residual serum rituximab levels ( $\mu\text{g/ml}$ ) measured in blood sample at M3 post-rituximab infusion using ELISA
  - Neutralizing anti-rituximab antibodies (ng/ml) measured in blood sample at M3 and M6 post-rituximab infusion
11. Responders are patients entered in partial or complete remission at M12. Relapse is defined by an increased proteinuria > 3.5 g/g after remission at M12. Patients from both groups will be analysed jointly. The risk factors studied will be the same as above measured at J0, M3, M6, M9 and M12 post-rituximab infusion.

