| Adverse Reaction (AR)       | 
An untoward and unintended response in a participant to an investigational medicinal product, which is related to, any dose administered to that participant.
 
The phrase "response to an investigational medicinal product" means that a causal relationship between a trial medication and an AE is at least a reasonable possibility, i.e. the relationship cannot be ruled out.
 
All cases judged by either the reporting medically qualified professional or the Sponsor as having a reasonable suspected causal relationship to the trial medication qualify as adverse reactions.
 |
| Serious Adverse Event (SAE) | 
A serious adverse event is any untoward medical occurrence that:
 
 
Results in death
 
Is life-threatening
 
Requires patient hospitalisation or prolongation of existing hospitalisation
 
Results in persistent or significant disability/incapacity
 
Consists of a congenital anomaly or birth defect.
 
                                                                                                                                                                                                                |

|                                                       |                                                                                                                                                                                                                                                                                                                                                                                                                                                       |
|-------------------------------------------------------|-------------------------------------------------------------------------------------------------------------------------------------------------------------------------------------------------------------------------------------------------------------------------------------------------------------------------------------------------------------------------------------------------------------------------------------------------------|

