### 10.3 Adverse Event Reporting

An adverse event is any condition that occurs after enrollment, whether or not considered related to study treatment. Signs and symptoms existing prior to study and documented on the baseline Medical History form or Physical Examination Form are not considered AEs. Only baseline signs and symptoms that worsen while the subject is on the study drug are considered adverse events.

At every visit, participant will be questioned regarding the occurrence and nature of any adverse experiences. If any signs, symptoms or the results of the laboratory tests indicate an adverse effect, the study physician should determine the severity (grade) of the AE and judge the relationship to the study treatment. In addition, if an adverse event necessitates medical care, appropriate care will be provided. Adverse events should be documented on the Adverse Event Report form, regardless of relationship to the study drugs. Notably, AEs thought to be due to treatment with the study drug are still reported as AEs in this study. The following information will be collected for all Adverse Events:

- Start and stop dates
- Severity (See the Severity Grading section below)
- Relationship to study drugs (See the Association with the Study Drug below )
- Action taken with study drugs
- Treatment for the AE and outcomes

The only circumstance in which an Adverse Event Report Form will not be filled out will be isolated lab value abnormalities of grade 1 severity.

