#### **10.10 Withdrawal of Study Participants**

The researchers may decide to withdraw the patient from the study if:

- The medical problem becomes worse.
- The researchers believe that participation in the research is no longer safe for the patient.
- The researchers believe that other treatment may be more helpful.
- The sponsor or the EMA stops the research for the safety of the participants.
- The sponsor cancels the research.
- The patient is unable to keep appointments or to follow the researcher's instructions.

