## **12. Statistical analysis**

### **12.1 Analysis strategy**

The statistical analyses will be performed by the biostatistician of the Delegation of Clinical Research and Innovation (DRCI) at the Nice center.

Before each analysis is performed, the conditions for the application of the tests that were used will be verified. The various tests will be considered significant at a threshold of 5% (unless otherwise specified). Continuous variables will be described using the number of observations (N), arithmetic mean (Mean), standard deviation, minimum (MIN), median (Median), and maximum (MAX) values. Categorical variables will be summarized by absolute (N) and relative frequencies (%). The statistical analysis will be performed using SAS Enterprise Guide 5.1 software (Copyright (c) 2012 by SAS Institute Inc., Cary, NC, USA). The statistical analysis will be performed using SAS Enterprise Guide 5.1 software (Copyright (c) 2012 by SAS Institute Inc., Cary, NC, USA).

Population analyzed:

The study patients will be analyzed according to the intention to treat principle (ITT). Each patient will be analyzed as a part of the group to which he or she was assigned at randomization.

A *per protocol* analysis will also be performed, though the results of this analysis cannot be substituted for those of the intention to treat analysis.

Missing data:

The “last observation carried forward” (LOCF) strategy will be used to impute the missing data for the principal objective and, when possible, for the secondary objectives.

Disposition of patients:

According to the CONSORT 2010 statements, a flow diagram of the progress through the phases (enrollment, allocation, follow-up, and analysis) of this study will be presented. The number of screening failures and reasons for screening failures will be summarized. The characteristics of patients lost to follow-up over the course of the study will be reported.

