### **12.3.2 Analysis of the main secondary objective:**

The secondary objectives consist in comparing several parameters between both treatment groups (GEMRITUX versus Personalized treatment) at different study timepoints according to each specific objective. The secondary assessment criteria can be grouped into two categories:

- Objectives 1, 2 and 3: binary criteria (remission clinical or immunological), compared at different timepoints between the two groups. Comparisons will be performed using a Chi-square test or Fisher's exact test in case of small sample.
- Objectives 4, 6 and 8: quantitative criteria compared at different timepoints between the two groups. Comparisons will be performed using a student t-test (or mann-whitney rank sum test in case of non-parametric variables).
- Objectives 5, 7: Quantitative criteria evolution (changes from baseline), defined as the difference between the  $M_x$  and  $D_0$  values,  $\Delta\text{variable} = \text{Variable } M_x - \text{Variable } D_0$ . Analyses will use an analysis of covariance which takes into account the initial values as a covariate. The dependent variable will be the  $\Delta\text{variable}$  and the variable of interest the treatment group.
- Objective 9: Severe infections will be described by type and their frequencies, absolute and relative, presented. The rate of patients presenting with at least one severe infection during follow-up will be compared between the two groups using a Chi-square test or Fisher's exact test in case of small sample.

Further multivariate analyses will be eventually discussed in case of imbalanced potential confounding factors between the groups.

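### The severe-infection endpoint is narrower than the protocol's own serious-event criteria, and its simple 24-month proportion makes no allowance for early withdrawal

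*Protocol*

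**What the plan says.** Secondary objective 9 in Section 2.2 is "Recording all AEs/SAEs during study follow-up, 24 months". In Section 3 the matching criterion becomes severe infection: "Severe infections are defined as infections that led to hospitalization during study follow-up". Section 12.3.2 describes these infections by type and frequency and then fixes one comparison: "The rate of patients presenting with at least one severe infection during follow-up will be compared between the two groups". The test named is chi-square, with Fisher's exact as the alternative when numbers are small. It is the only between-arm test of adverse events in the protocol. No observation time, censoring or handling of death is mentioned. Section 12.1 analyses patients as randomised and applies LOCF to secondary objectives where possible.

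Section 10.1 defines a serious adverse event more widely. Besides "Requires patient hospitalisation or prolongation of existing hospitalisation", it lists death and life-threatening events. Section 10.5 has investigators report all SAEs to the sponsor, and Section 10.3 records "Start and stop dates" for every adverse event.

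Section 10.10 lets the researchers withdraw a patient from the study on several grounds, among them "The medical problem becomes worse" and the belief that another treatment may help more. The list is the same for both arms. Section 10.11 excludes women who become pregnant. Section 8.5 requires visits to continue in one situation only: active disease with anti-PLA2R1 and anti-rituximab activity at relapse. Section 7.2 allows for 10% loss to follow-up overall, regards it as minor, and does not split it by arm.

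**The concern.** There are two separate weaknesses.

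The first is the definition. The personalised strategy gives some patients rituximab earlier and at a higher dose than the control strategy, so infection is a central harm question. Yet the rule that decides what counts asks only whether the infection caused an admission. An infection that kills at home, or that arises in hospital and prolongs the stay, is serious under Section 10.1 but not severe under Section 3. The test would record that patient as having no severe infection.

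The second is observation time. A patient who leaves infection-free at M6 stays in the denominator as a non-event for all 24 months. This lowers the proportion in any arm that loses patients. If one arm loses more patients than the other, it also shifts the contrast towards an apparent excess of infections in the arm followed longer.

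**Working it through.** **Step 1: the two definitions side by side.**

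| Infection | Severe under Section 3? | Serious under Section 10.1? |
|---|---|---|
| Causes admission, fatal or not | Yes | Yes |
| Fatal, no admission | No | Yes (death) |
| Life-threatening, no admission | No | Yes (life-threatening) |
| Acquired in hospital, prolongs the stay | No | Yes (prolongation) |

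The last three rows are the gap. The protocol gives no infection rate, so their frequency cannot be estimated and there is no stated figure to reproduce. Their leverage can be shown: 64 patients randomised 1:1 give 32 per arm, and one reclassified patient moves an arm's proportion by 1/32 = 3.1 points.

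**Step 2: effect of early withdrawal on the proportion.** Assumptions, none from the protocol: the same constant infection hazard in both arms, 24-month risk *r*, and a share *w* of patients leaving at month *m*, independently of infection.

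- Hazard per month: h = −ln(1 − r)/24
- Risk up to withdrawal: 1 − exp(−h·m)
- Observed proportion: (1 − w)·r + w·[1 − exp(−h·m)]

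For r = 25%, m = 6: h = 0.2877/24 = 0.01199, and the 6-month risk is 1 − exp(−0.0719) = 6.94%.

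- w = 20% (controls): 0.80 × 25% + 0.20 × 6.94% = 21.4%
- w = 5% (personalised): 0.95 × 25% + 0.05 × 6.94% = 24.1%
- False difference: 2.7 points, or 0.87 of a patient in 32
- w = 10% in both arms: 0.90 × 25% + 0.10 × 6.94% = 23.2% in each. There is no false difference, but the true 25% is understated by 1.8 points.

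For r = 15%, m = 6: the 6-month risk is 3.98%. The proportions are 12.8% (w = 20%) and 14.4% (w = 5%), a false difference of 1.7 points before rounding, or 0.53 of a patient in 32.

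**Step 3: wider scenarios, same formula.**

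| r | Withdrawn, personalised / control | Month | Observed, personalised / control | Ratio | Patients per 32 |
|---|---|---|---|---|---|
| 20% | 10% / 10% | 12 | 19.1% / 19.1% | 1.00 | 0 |
| 20% | 5% / 15% | 12 | 19.5% / 18.6% | 1.05 | 0.3 |
| 20% | 5% / 30% | 12 | 19.5% / 17.2% | 1.14 | 0.8 |
| 20% | 5% / 30% | 6 | 19.3% / 15.6% | 1.23 | 1.2 |
| 20% | 20% / 55% | 12 | 18.1% / 14.8% | 1.22 | 1.1 |
| 30% | 5% / 30% | 6 | 28.9% / 23.6% | 1.23 | 1.7 |

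The fifth row is an extreme case in which every expected non-remitter leaves at M12 (100 − 80 = 20% and 100 − 45 = 55%, from Sections 7.1 and 7.2). For *r* from 10% to 30%, the false difference across the uneven scenarios is 0.5 to 5.4 points.

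**Step 4: effect on the test.** The exact rejection probability of Fisher's test at 32 per arm was computed for three uneven scenarios. The largest was 4.7%, against 2.8% with no withdrawal, still below the 5% threshold in Section 12.1. The effect is on the estimate more than on the p-value.

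**The case against.** A reader might infer that follow-up is unequal by rule and that the infection contrast is therefore biased against the personalised arm. The documents do not support this. The withdrawal grounds are the same in both arms and discretionary, and the expected loss is 10% overall. Heavier withdrawal among controls is an inference from the expected remission rates of 80% and 45% and from the absence of rituximab before M6 in that arm. Even that inference weakens at M6, when controls with active disease are due to receive rituximab. The 20% and 5% example averages 12.5%, above the planned loss. All of this stands, so the bias is a possibility and not a finding.

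A second objection is that a time-to-event analysis would not cure the problem. If worsening disease drives withdrawal, and Section 10.8 lists severe infection among events linked to the disease, then censoring at withdrawal is informative. Rituximab also starts at different times in the two arms, so a single hazard ratio would be hard to interpret. This stands too. It argues against replacing the planned test, but not against adding descriptive summaries that show observation time.

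Third, a proportion with at least one event is a standard safety summary in a 64-patient trial, and exposure-adjusted rates are often left to a SAP. That is fair for the second weakness. It does not answer the first, because the protocol itself fixes the narrow definition.

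Finally, it would be too broad to say that the endpoint misses fatal infections. A fatal infection that led to admission counts. The omitted cases are still reported as SAEs, and Section 14 sends deaths to the monitoring committee. They are lost to the comparison, not to safety oversight.

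**Conclusion.** The definition gap is certain on the text and is the main point. The one planned between-arm adverse-event test can class a patient with a fatal or stay-prolonging infection as free of severe infection, contrary to the protocol's own serious criteria. Nothing shows that the gap favours either arm, and its frequency cannot be estimated from the protocol.

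The observation-time point is secondary. Any early withdrawal makes the proportion understate the 24-month risk, by 1.8 points in the equal-loss example. The contrast is distorted only if withdrawal differs by arm. The size is then about 2 to 3 points, under one patient per 32, with 20% against 5% leaving at M6, and at most 5.4 points (1.7 patients per 32) in the most uneven scenarios tried. These figures rest on assumed risks of 10% to 30%, assumed withdrawal shares and times, and equal constant hazards unrelated to withdrawal. A reader should not conclude that the planned contrast is biased, only that it may be. This is a low-severity improvement that costs little.

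**What to change.** In Section 3, define a severe infection as one that is fatal, is life-threatening, or leads to or prolongs hospitalisation, and refer to Section 10.1 so that the two stay aligned.

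In Section 12.3.2, keep the chi-square or Fisher comparison and add two summaries by arm from the recorded dates: severe infections per patient-year, and the cumulative incidence of first severe infection to 24 months. State that censoring at withdrawal may be informative, and report the number and timing of withdrawals by arm beside these summaries.

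The cost is wording, a few more events to classify and a little extra analysis. Event dates and SAE reports are already collected, so no new data are needed. Continuing safety contact to M24 after withdrawal would address the observation-time problem more directly, but it changes study conduct and is not needed for this fix.

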### **13. Feasibility**

This protocol is supported by the *Centre de Référence Maladie rare "Syndrome néphrotique"* (see annexe).

The centers participating in this network follow about 2 new MN patients each year. In order to achieve the objective of recruiting 64 patients in four years, 22 centers will have to actively recruit on average one patient each year.

Moreover, the experience from the PHRC GEMRITUX (NCT01508468) and the PHRC PRAM-KT (PHRC2011-A01302-39, NCT01897961) showed the ability of our centers to recruit such patients. We are currently conducting an observational study (SOURIS 2014-A00886-41) involving 5 centers that recruited 33 patients in 2 years with the same inclusion criteria.

### **14. Independent data-monitoring committee**

The independent data monitoring committee is a consultative committee charged with advising the study sponsor on the benefit/risk ratio of the conduct of a clinical trial.

Its members, all competent in the conduct of clinical trials (pathology, methodology...) are not directly involved in the study.

The selection of its membership is made by the sponsor in collaboration with the coordinating investigator.

They are nominated by the sponsor and their term of office corresponds to the length of the study.

They undertake their duties voluntarily, and agree to respect the confidentiality of the study data.

The committee will receive all versions of the protocol, the annual safety report, and may be consulted at any time by the sponsor if a suspected unexpected severe adverse reaction or unwanted effect is particularly difficult to analyze, and/or if the data may change the apparent risk/benefit ratio during the course of the study.

The committee will analyze the data sent to it, and may demand additional information. It then makes a recommendation about the future of the study (continue, modify, halt etc).

The committee will meet annually.

Each associate investigator declaring one of the following events:

- commencement of supportive renal dialysis,
- or a non-fatal cardiovascular event: myocardial infarct, cerebrovascular accident, coronary or peripheral revascularization procedure, amputation, hospitalization for heart failure, cardiac arrest and resuscitation),
- or cardiovascular mortality,
- or non-cardiovascular mortality.

will complete a specific form and supply a hospital summary or consultation record that documents the event. These documents will be sent to the Nice DRCl, who will pass them to the independent data monitoring committee before each of its annual meetings.

If there is evidence that brings the safety of the study intervention into question is identified, the protocol may be suspended.

## **15. Study resources**

### **Biology**

The greatest part of the requested budget is devoted to develop new tests: epitope profile characterization, B and T cells count with TReg and Memory B cells, immunomonitoring of rituximab, cytokine profile determination. To these purposes, a 50% of lab technician will be employed.

### **Study coordination and the analyses of the results**

A 50% of Study Coordinator will be employed at the coordinating center for the duration of the study. His tasks will be to coordinate the study, collect and enter data onsite.

In all investigators' centers, one vacation per month clinical research assistant for each visit of patient will be dedicated for data collection and data entry.

A budget is dedicated:

- for the creation of the database, the data management and the statistical analyses performed by a data manager and a statistician,
- for the monitoring by a monitor,
- for the ethical and logistical follow-up by a project manager,
- for the data safety by a pharmacist.

For the data committee, a budget will be allocated to the 4 members for their participation (one committee by year).

